## Abstract

**Background:**

The optimal treatment of early stage follicular Lymphoma is a matter of debate. Radiation therapy has frequently been applied with a curative approach beside watchful waiting. Involved field, extended field and total nodal radiation techniques are used in various protocols, but the optimal radiation field still has to be defined. Follicular lymphoma is characterized by stable expression of the CD20 antigen on the tumour cells surface. The anti CD20 antibody Rituximab (Mabthera^®^) has shown to be effective in systemic therapy of FL in primary treatment, relapse and maintenance therapy.

**Methods/design:**

The MIR (Mabthera^® ^and Involved field Radiation) study is a prospective multicenter trial combining systemic treatment with the anti CD20 antibody Rituximab (Mabthera^®^) in combination with involved field radiotherapy (30 - 40 Gy). This trial aims at testing the combination's efficacy and safety with an accrual of 85 patients.

Primary endpoint of the study is progression free survival. Secondary endpoints are response rate to Rituximab, complete remission rate at week 18, relapse rate, relapse pattern, relapse free survival, overall survival, toxicity and quality of life.

**Discussion:**

The trial evaluates the efficacy of Rituximab to prevent out-filed recurrences in early stage nodal follicular lymphoma and the safety of the combination of Rituximab and involved field radiotherapy. It also might show additional risk factors for a later recurrence (e.g. remission state after Rituximab only).

**Trial Registration:**

ClinicalTrials (NCT): NCT00509184

## Background

Worldwide, follicular lymphoma (FL) is the second most common type of non-Hodgkin's lymphoma (NHL) [1] with a rapidly increasing incidence in the last decades [2].. In the group of indolent lymphomas, FL is the most common type with 70% of cases. FL tumor cells are characterized by the translocation t (14;18)(q32;q21)and invariably express the CD20 antigen. The WHO Classification differentiates between grade I, II and III follicular lymphoma in respect to the number of centroblasts in the visual microscopy field. FL grade III is often regarded as an aggressive lymphoma and treated accordingly. Most patients are diagnosed in advanced disease stage and cannot be cured with conventional therapy. However, 15-30% patients are diagnosed in the limited Ann Arbor stages I and II and are potential candidates for a curative treatment approach. Standard of treatment for patients with limited disease with a curative intention is radiotherapy. However, no consensus of the required radiation field has been reached. Table 1 depicts the results of various radiotherapy trials in FL lymphoma in stage I and II. Most of the trials are retrospective analysis. Involved field (IF), extended field (EF) and total nodal (TN) irradiation techniques have been applied. The relapse free survival rate after 10 years was between 38% and 72% and the 10 year overall survival ranged in between 50% and 78%. Median survival was above 12 years, however, in some of the international trials which categorized lymphomas according to the Working Formulation also FL grade III and mantle cell lymphoma were part of the analysis. Forty-one percent of the patients had a relapse after 8 years in a prospective German observation trial with 117 patients with early stage FL who were treated with EF or TN. In stage I patients, there was no relapse in the irradiation field after 7 years, but 15% out of filed relapses. This trial led to the conclusion that large volume radiation techniques may prevent relapses. However, as extensive radiation protocols are associated with significant toxicities, grade 3 and grade 4 adverse events concerning the hematopoietic system were observed in 22% of patients [3].

There have been several studies which combined radiation therapy with systemic chemotherapy in early stage FL. Most studies failed to demonstrate a benefit of combined therapy [4-7]. In one study, the sequential administration of COP, CHOP-B and involved field irradiation improves relapse free survival, but not overall survival in comparison to historical cohort. Relapse free survival after 10 years was 72%, however 22% of patients experienced a grade IV neutropenia and 14 secondary malignancies were observed [8,9].

The monoclonal chimeric anti CD 20 antibody Rituximab has revolutionized the treatment of FL in the last decade. The pivotal phase II trial tested Rituximab monotherapy in 37 patients with refractory or relapsed FL. The overall response rate (ORR) was 46% with 8% complete responses (CR). The median time to progression (TTP) reached 10.2 months [10]. These promising results as well as other phase II clinical trials demonstrated a significant single agent activity of Rituximab in pretreated as well as in previously untreated patients with FL [11-13].. In combination with CHOP chemotherapy, Rituximab induced responses in all evaluable patients with a complete remission (CR) rate of 63% and a median PFS of 82 months in a Phase II trial [14]. These results were confirmed in four prospective randomised phase III studies investigating Rituximab in combination chemotherapy versus chemotherapy alone in first line therapy which showed significant increase in initial response rates, a significant prolongation of response duration and a significantly longer overall survival [15-18]. Rituximab was added to FCM (Fludarabine, Cyclophosphamde, Mitoxantrone) chemotherapy in relapsed FL in a prospective randomized Phase III trial and showed a significantly longer PFS and OS compared with FCM alone [19]. In addition to the impressing results of Rituximab as part of first line and relapse treatment, Rituximab maintenance therapy is effective in relapsed FL [20-22]. Rituximab maintenance therapy has also been shown to prolong PFS after first line therapy in two prospective randomized trials [23,24].

In the context of radiotherapy, the high efficacy of Rituximab in systemic treatment suggests that this drug may be of benefit in the eradication of minimal disease outside the radiation field. This concept is in line with the observation that Rituximab contributes to the elimination of minimal residual disease after cytotoxic therapy [25-27]. In addition, Rituximab may enhance radiosensitivity of lymphoma cells and may thus improve the efficacy of radiotherapy [28,29].

### On-site monitoring

During recruitment of patients monitoring on site is performed according to good clinical practice (GCP) guidelines. The data management will be performed by the Coordination Centre for Clinical Trials (KKS) of the University of Heidelberg.

### Ethics, informed consent and safety

The final protocol was approved by the ethics committee of the University of Heidelberg, Medical School (AFmu-085/2007, http://www.klinikum.uni-heidelberg.de) and the Paul-Ehrlich-Institute (PEI-registration number 432/06). This study complies with the Helsinki Declaration in its recent German version, the Medical Association's professional code of conduct, the principles of Good Clinical Practice (GCP) guidelines and the Federal Data Protection Act. The trial will also be carried out in keeping with local legal and regulatory requirements. The medical secrecy and the Federal Data Protection Act will be followed.

Written informed consent is obtained from each patient in oral and written form before inclusion in the trial and the nature, scope, and possible consequences of the trial have been explained by a physician. The investigator will not undertake any measures specifically required only for the clinical trial until valid consent has been obtained.

### Study design and endpoints

The MIR study is a prospective phase II study combining systemic Rituximab therapy with involved field irradiation in patients with FL WHO Grad 1 and 2 in Stage I and II.

This trial aims at testing the combination's efficacy and toxicity with an accrual of 85 patients.

Primary endpoint of the study is progression free survival (2 years). Secondary endpoints are complete remission rate after Rituximab monotherapy (week 7) and after complete treatment (week 18), relapse rate, relapse pattern, relapse free survival, overall survival, toxicity and quality of life.

### Patient selection

In order to be included in the MIR trial, patients (18 to 75 years) are required to have pathologically documented FL Who grade 1 or 2 in Ann Arbor Stage I or II. The histology has to be confirmed by one of the reference pathologists of the GLSG. Evaluation of CD20 status is compulsory. Maximal tumour diameter is 7 cm. Accrued patients will be expected to demonstrate sufficient compliance, they should also live in relative proximity of the centre of care to ensure adequate follow-up after treatment. In addition, adequate haematological function is essential for inclusion in the trial (leukocytes ≥ 3000 × 10^3 ^/ml, platelets ≥ 100000 × 10 ^3 ^/ml, and haemoglobin ≥ 10 g/dL). Patients are required to use adequate contraception during and at least up to 3 months after treatment. Naturally, written informed consent is obtained prior to commencement of treatment in this trial.

Patients are not eligible with previous irradiation, chemotherapy of immunotherapy. Patients with severe concurrent systemic disease or other malignant disease (apart from cervical carcinoma in-situ, basal cell carcinoma, or unless previously treated and in remission for ≥ 5 years without further treatment) can also not be included in this trial. Furthermore, clinical performance worse than ECOG 2, bulky disease (> 7 cm), splenic involvement, immunodeficiency, viral hepatitis, collagenosis, severe psychiatric illness, hypersensitivity to foreign proteins will prohibit inclusion as will pregnancy or breast feeding.

### Statistical Design

The hypothesis states an improvement of the progression free survival after 2 years from 75% to 89% (risk reduction by 40% using Rituximab). 77 patients have to be evaluated to proof the hypthesis with a 95% power using a single arm binomial test. An additional 8 patients have to be recruited for a possible 10% drop-out rate.

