### Trial duration

Patient recruitment is planned to be completed after 24 months. Patients will be monitored for two and a half years after study entry. The total duration of the trial is estimated to be 4 and a half years. Recruitment started in March 2008. As of February 2010, 65 patients have been included in the trial.

Individual exclusion criteria are serious adverse reactions or the patient's voluntary withdrawal from the trial.

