### Assessment of therapeutic efficiency

CT or MRI of the involved regions are scheduled for week 7 and 18. For screening of the whole body stem, CT or MRI imaging is planned for months 6, 12, 18, 24 and 30 after start of therapy. At all above mentioned follow-up visits, there is also a clinical examination with palpation of all lymph node sites schedulded.

Local response is evaluated in accordance with the Cheson Criteria [30].

• **Complete response (CR) **is the complete disappearance of all detectable evidence of disease on CT, and all disease-related symptoms, and normalization of biochemical abnormalities, and normal bone marrow biopsy (BMB). Previously involved nodes on CT more than 1.5 cm in their greatest axial diameter must regress to less than 1.5 cm, and previously measured nodes of 1.1-1.5 cm must decrease to less than 1 cm.

• **CRu (uncertain) **corresponds to CR criteria but with a residual mass more than 1.5 cm in greatest axial diameter that has regressed by more than 75%.

• **Partial response (PR) **is at least 50% reduction in the sum of the product of the greatest diameters (SPD) of the six largest nodes with no increase in the size of other nodes and no new sites of disease. Splenic and hepatic nodules must regress by at least 50% in the SPD.

• **Stable disease (SD) **is less than a PR but is not progressive disease. Progressive disease (PD) is more than 50% increase in the sum of the product of the greatest diameters of any previously abnormal node, or appearance of any new lesions during or at the end of therapy.

• **Relapsed disease (RD) **is the appearance of any new lesion or increase in size of more than 50% of previously involved sites or nodes in patients who achieved CR or CRu.

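### The stated primary test, a binomial test of 2-year PFS in 77 evaluated patients, has about 92% power rather than 95%; a Kaplan-Meier 2-year test on all 85 recovers most of the gap

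*Protocol article*

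**What the plan says.** Under Study design and endpoints, the protocol article fixes a landmark: "Primary endpoint of the study is progression free survival (2 years"). Statistical Design gives the planning values: "The hypothesis states an improvement of the progression free survival after 2 years from 75% to 89" per cent, described there as "risk reduction by 40% using Rituximab". The test and the number follow: "77 patients have to be evaluated to proof the hypthesis with a 95% power using a single arm binomial test". Drop-out is handled by recruiting more: "An additional 8 patients have to be recruited for a possible 10% drop-out rate", which makes 85.

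Follow-up runs past the landmark. Trial duration says "Patients will be monitored for two and a half years after study entry", and Assessment of therapeutic efficiency says "CT or MRI imaging is planned for months 6, 12, 18, 24 and 30 after start of therapy". The binomial test is the only primary test that the article names. It gives no significance level.

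**The concern.** A patient who leaves at month 18 without progression has contributed 18 months of information on 2-year PFS. A binomial test on patients with a known 2-year status cannot use it. The plan replaces such patients instead of analysing them, although a standard estimator of the same quantity would use all 85.

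The binomial test is also discrete. With 77 patients its true size falls well below the nominal level, and a normal-approximation sample size does not allow for that. The stated 95% power may therefore not hold for the named test in its exact form. At stake are a few points of power and an inaccurate power statement.

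**Working it through.** **Inputs.** From Statistical Design: p0 = 0.75, p1 = 0.89, 77 evaluated, 8 added, 10% drop-out, 95% power. Assumed because not stated: the significance level, the shape of the PFS curve (exponential unless noted) and the timing of drop-out (exponential, 10% by month 24).

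**1. Reproducing 77.** For one proportion by the normal approximation, n = [(z_alpha·√(p0·q0) + z_power·√(p1·q1)) / (p1 − p0)]².
- One-sided 5%: [(1.645·√0.1875 + 1.645·√0.0979) / 0.14]² = 76.8, so 77. This matches the plan.
- One-sided 2.5%: 94.8, so 95. This does not match.

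One-sided 5% is therefore used as the main case. For drop-out, 77 × 1.10 = 84.7, so 85, also as planned.

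**2. Exact power of the named test.** With n = 77 and p0 = 0.75:

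| Progression-free needed | True size | Power at 89% |
|---|---|---|
| at least 65 | 3.3% | 92.3% |
| at least 66 | 1.7% | 86.4% |

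The first row is the one-sided 5% test and the second the one-sided 2.5% test. At one-sided 5% the exact test falls 95 − 92.3 = 2.7 points short of the stated power.

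**3. When the evaluable number is random.** I took 85 recruited with 10% drop-out and applied the exact test to patients whose 2-year status is known (progressed before leaving, or followed to 24 months). On average about 77 are evaluable. Power is about 91% (90.9%) and size about 2.4%. Both are lower than with a fixed 77. One reason is that patients who progress before leaving are counted, while those who leave progression-free are not.

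**4. Kaplan-Meier 2-year test on all 85.** Z = [ln(−ln S(24)) − ln(−ln 0.75)] / SE, where S(24) is the Kaplan-Meier estimate and SE is the square root of the Greenwood sum divided by |ln S(24)|. Reject if Z ≤ −1.645. By simulation, power is about 94.4% and size about 4%. Size stays at about 4% for Weibull curves through 75% at 24 months with shapes from 0.44 to 1.2.

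**5. Gain.** 94.4 − 92.3 = 2.1 points against a fixed 77, and 94.4 − 90.9 = 3.5 points against the random evaluable subset. With 77 patients and no drop-out, the Kaplan-Meier test has about the same power as the binomial test (92.3%). The gain therefore comes from bringing in the other patients' follow-up, which also brings the true size nearer to 5% (about 4%, against 3.3% or 2.4%).

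**6. One-sample log-rank alternative.** With the reference hazard −ln(0.75)/24 = 0.0120 per month:
- 77 patients, cut at 24 months: 93.3% power. Using event times alone is worth about 1 point over 92.3%.
- 85 patients, followed to month 30: 97.5 to 97.7%, depending on the drop-out pattern assumed.

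The second figure rests on a constant hazard, which gives 0.75⁴ = 32% progression-free at 8 years. The Background section reports that 41% had relapsed by 8 years in the prospective observation trial (about 59% relapse-free), and 10-year relapse free survival of 38% to 72%. A Weibull curve through 75% at 24 months needs these shapes:
- 59% at 8 years: ln[ln 0.59 / ln 0.75] / ln 4 = 0.44.
- 38% at 10 years: ln[ln 0.38 / ln 0.75] / ln 5 = 0.75.

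Both imply a falling hazard. Under them, the nominal 5% log-rank test to month 30 has a true size of 7.1% and 5.7% respectively.

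**The case against.** **The final analysis is inferred.** The binomial test appears only in the sample-size sentence of a condensed article. An unseen analysis plan may specify a time-to-event analysis, and nothing says outright that drop-outs' data will be discarded. That is fair. But this is the only primary test that the article states, and it is stated on evaluated patients. The point is about that test, not about something left out.

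**The loss is small.** Binomial power stays above 90% at one-sided 5% if 89% is true, and part of the shortfall is discreteness. Both stand, and they limit the weight of the point.

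**A reader might infer a much larger cost, 5 to 12 points, from reducing PFS to a yes/no status.** The documents do not support that.
- Dichotomising alone costs about 1 point. About 5 points (97.5 − 92.3) appear only when months 24 to 30 are added, which changes the 2-year endpoint.
- Twelve points need either one-sided 2.5% with drop-outs removed (82.4% against 94.2%), a level at which 77 does not reproduce, or a true 2-year PFS of 85% (63.2% against about 75 to 77%). The 85% comes from reading the quoted 40% as a reduction of the 25% risk. The plan's 89% fits a hazard ratio of 0.40 instead (0.75^0.4 = 89.1%).

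**A reader might also infer that the month 24 to 30 data are wasted.** Relapse rate, relapse pattern, relapse free survival and overall survival are secondary endpoints and can use them.

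**The trial is under way.** Trial duration reports 65 patients included by February 2010. In a single-arm trial, a change of primary test must be fixed and dated before the 2-year outcomes are examined. This stands as a condition on the fix.

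**Conclusion.** The point holds as a modest matter of efficiency and of accurate reporting. Under one-sided 5% and a true 2-year PFS of 89%, the named test has 92.3% exact power on 77 patients and about 91% on the evaluable subset of 85, against the stated 95%. A Kaplan-Meier 2-year test on all 85 has about 94.4%, a gain of about 2 to 3.5 points. It keeps the endpoint and the 75% benchmark.

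The 92.3% depends only on the assumed level. The 91% and 94.4% also depend on 10% drop-out unrelated to outcome and, less sensitively, on the shape of the PFS curve. The results do not justify making a log-rank test to month 30 primary, because its reference curve would have to be invented and the Background figures point away from a constant hazard.

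**What to change.** In Statistical Design:

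- Make the primary test a comparison of the Kaplan-Meier 2-year PFS estimate with 75%, on the complementary log-log scale, in all 85 patients. Censor drop-outs at their last assessment and report the confidence interval. Say that progression found at the scheduled month-24 scan counts as an event by 2 years.
- Restate the power with the significance level it refers to: at one-sided 5%, about 94% for this test on 85. If the binomial test is kept, state about 92% for the exact test on 77.
- Add a one-sample log-rank test to month 30 as a supportive analysis only, if wanted, with its reference curve stated and justified.

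The change needs no extra patients, visits or scans. Its costs are reliance on non-informative censoring and on a large-sample approximation, and a dated amendment made before the 2-year results are examined.

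### On 77 patients, no cut-off of the binomial test gives the stated 95% power with a true type I error of 5% or less; at the 5% level the exact power is about 92%

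*Protocol article*

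**What the plan says.** All the relevant text is in the Statistical Design section of the protocol article. The effect is given as "The hypothesis states an improvement of the progression free survival after 2 years from 75% to 89" per cent. The sample size sentence reads "77 patients have to be evaluated to proof the hypthesis with a 95% power using a single arm binomial test". It is followed by "An additional 8 patients have to be recruited for a possible 10% drop-out rate", which brings the total to the 85 given under Study design and endpoints. That section also makes 2-year progression-free survival the primary endpoint, so this is the power statement for the trial's main test.

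The article gives no significance level, sidedness or critical value, and does not say whether the binomial test is exact or a large-sample approximation. A journal article commonly leaves these details to the full protocol, so their absence is not the point here. It does mean that the level must be inferred before the figure can be checked.

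**The concern.** A binomial test on 77 patients has a discrete outcome. Its pass mark can only be a whole number of patients, and each pass mark has one true type I error and one true power. A formula based on the normal curve ignores this and can report a combination of error and power that no actual pass mark attains. The combination here, 95% power at an apparent 5% level, looked like such a case.

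The consequence is limited but concerns the primary test. Either the trial has somewhat less power than stated, or its pass mark allows a somewhat higher chance of a false positive than 5%. The two options differ by one patient (64 or 65 of 77), and the pass mark should be settled before outcomes are analysed.

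**Working it through.** **Inputs.** From Statistical Design: null rate p0 = 0.75, alternative p1 = 0.89, n = 77 evaluable, power 95%, single-arm binomial test, 8 further patients. Assumed: one-sided 5%. The check uses the two stated percentages and not the accompanying phrase "risk reduction by 40% using Rituximab".

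**Step 1: reproduce the plan's figure.** The usual normal-approximation formula for one proportion is

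n = [(z_alpha × √(p0(1 − p0)) + z_power × √(p1(1 − p1))) / (p1 − p0)]²

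with √(0.75 × 0.25) = 0.4330 and √(0.89 × 0.11) = 0.3129.

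- One-sided 5%: [(1.645 × 0.4330 + 1.645 × 0.3129) / 0.14]² = 76.8, so 77. Power at n = 77 is 95.05%.
- Two-sided 5%: [(1.960 × 0.4330 + 1.645 × 0.3129) / 0.14]² = 94.8.
- One-sided 10%: [(1.282 × 0.4330 + 1.645 × 0.3129) / 0.14]² = 58.4.
- One-sided 5% by other approximations: arcsine 78.6, continuity-corrected 83.8.

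Of these, only the uncorrected normal approximation at one-sided 5% returns 77.

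**Step 2: true operating characteristics on 77 patients.** Let X be the number alive and progression-free at 2 years. The type I error of the rule X ≥ r is P(X ≥ r | 0.75), and its power is P(X ≥ r | 0.89), both from the binomial distribution.

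| Success if | True one-sided error | True power |
|---|---|---|
| ≥ 63 of 77 | 10.3% | 98.0% |
| ≥ 64 of 77 | 6.1% | 96.0% |
| ≥ 65 of 77 | 3.3% | 92.3% |
| ≥ 66 of 77 | 1.7% | 86.4% |

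No row has error at or below 5% and power at or above 95%. Both quantities fall as the pass mark rises, so pass marks outside the table do not help.

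**Step 3: where the normal approximation puts the pass mark.** For 64 of 77, the observed rate is 0.83117 and the null standard error is √(0.1875 / 77) = 0.04935, so z = 0.08117 / 0.04935 = 1.64488. The critical value is 1.64485, so p = 0.049997 and the z-test just rejects. Its pass mark is therefore 64, with true error 6.1%. The exact test needs 65, with power 92.3%.

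**Step 4: nearby sample sizes, exact test at one-sided 5%.**

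| Evaluable | Success if | True error | Power |
|---|---|---|---|
| 76 | ≥ 64 | 3.8% | 92.9% |
| 77 | ≥ 65 | 3.3% | 92.3% |
| 79 | ≥ 66 | 4.8% | 95.1% |
| 85 | ≥ 71 | 4.1% | 95.6% |

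The smallest number reaching 95% is 79. Because power moves in a saw-tooth, it stays at or above 95% only from 89 onwards.

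**The case against.** The strongest reply is that nothing has been miscalculated. The standard formula returns exactly 77 and 95%, the article never uses the word exact, and the z-test that matches the formula has true power of 96.0%. A mid-p test also rejects at 64 of 77 (mid-p = 0.0332 + ½ × (0.0608 − 0.0332) = 0.047). This stands in part: the power is not lost under every form of the test. But those forms reach 95% by using the pass mark of 64, whose true error is 6.1%. The reply moves the discrepancy from power to type I error and does not remove it.

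The gap is also small. It comes from discreteness, two more evaluable patients would close it, and 92% rather than 95% planned power would hardly change a phase II decision. That is accepted and sets the weight given to the point.

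A reader might infer more, and the documents do not support it:

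- *That power is only 86%, or that the chance of missing a real effect is as high as 14%.* This needs a two-sided 5% level. The article states none, and its sample size does not fit one: the same formula would ask for 94.8 patients.
- *That the pass mark is undetermined because no level is printed.* The full protocol may give it, and an article may leave it there.
- *That the drop-out allowance is wrong.* Dividing 77 by 0.9 gives 85.6 rather than 85, but adding 10% (77 × 1.10 = 84.7) is a common convention. Ending with 76 evaluable gives exact power of 92.9%, so nothing is lost.
- *That the binomial test should give way to a Kaplan-Meier analysis.* That is a preference and does not follow from this check.

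**Conclusion.** The point holds as a minor correction. A binomial test on 77 patients that keeps its true one-sided error at or below 5% has at most 92.3% power for 75% against 89%, which is 2.7 points below the stated 95%. A pass mark that does exceed 95% power (64 of 77) has a true error of 6.1%, which is 1.1 points above 5%.

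This rests on two assumptions. The first is that the intended level is one-sided 5%, inferred from the match with the formula. If the full protocol sets a one-sided level of 6.1% or more, the 95% would be met, although the formula would then not have led to 77 at a level such as 10% (58.4). The second is that 2-year status is known for every patient counted, as the planned test implies.

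**What to change.** In Statistical Design, name the exact binomial test at one-sided 5%, give success as at least 65 of 77 evaluable patients, and restate the power as about 92% (true error 3.3%). Because the pass mark moves with the number evaluable, add that it will be the smallest count whose exact error is at most 5% for the number actually evaluated, for example 64 of 76 or 71 of 85. If 2-year status is obtained for all 85 enrolled, the rule of at least 71 of 85 restores power to 95.6% with error 4.1%.

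The cost is a change of wording and a slightly less favourable power figure. No patients are added, and the endpoint and type of test stay as planned.
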